# A multicentre, randomised controlled trial to compare the clinical and cost-effectiveness of Lee Silverman Voice Treatment versus standard NHS Speech and Language Therapy versus control in Parkinson’s disease: a study protocol for a randomised controlled trial

**DOI:** 10.1186/s13063-020-04354-7

**Published:** 2020-05-27

**Keywords:** Idiopathic Parkinson’s disease, Lee Silverman voice treatment, Speech and language therapy, Randomised controlled trial, Dysarthria

## Abstract

**Background:**

Parkinson’s disease (PD) affects approximately 145,519 people in the UK. Speech impairments are common with a reported prevalence of 68%, which increase physical and mental demands during conversation, reliance on family and/or carers, and the likelihood of social withdrawal reducing quality of life. In the UK, two approaches to Speech and Language Therapy (SLT) intervention are commonly available: National Health Service (NHS) SLT or Lee Silverman Voice Treatment (LSVT LOUD®). NHS SLT is tailored to the individuals’ needs per local practice typically consisting of six to eight weekly sessions; LSVT LOUD® comprises 16 sessions of individual treatment with home-based practice over 4 weeks. The evidence-base for their effectiveness is inconclusive.

**Methods/design:**

PD COMM is a phase III, multicentre, three-arm, unblinded, randomised controlled trial. Five hundred and forty-six people with idiopathic PD, reporting speech or voice problems will be enrolled. We will exclude those with a diagnosis of dementia, laryngeal pathology or those who have received SLT for speech problems in the previous 2 years. Following informed consent and completion of baseline assessments, participants will be randomised in a 1:1:1 ratio to no-intervention control, NHS SLT or LSVT LOUD® via a central computer-generated programme, using a minimisation procedure with a random element, to ensure allocation concealment. Participants randomised to the intervention groups will start treatment within 4 (NHS SLT) or 7 (LSVT LOUD®) weeks of randomisation.

Primary outcome: Voice Handicap Index (VHI) total score at 3 months. Secondary outcomes include: VHI subscales, Parkinson’s Disease Questionnaire-39; Questionnaire on Acquired Speech Disorders; EuroQol-5D-5 L; ICECAP-O; resource utilisation; adverse events and carer quality of life. Mixed-methods process and health economic evaluations will take place alongside the trial. Assessments will be completed before randomisation and at 3, 6 and 12 months after randomisation.

The trial started in December 2015 and will run for 77 months. Recruitment will take place in approximately 42 sites around the UK.

**Discussion:**

The trial will test the hypothesis that SLT is effective for the treatment of speech or voice problems in people with PD compared to no SLT. It will further test whether NHS SLT or LSVT LOUD® provide greater benefit and determine the cost-effectiveness of both interventions.

**Trial registration:**

International Standard Randomised Controlled Trials Number (ISRCTN) Registry, ID: 12421382. Registered on 18 April 2016.

## Background

In prevalence and years lived with disability, Parkinson’s disease (PD) is the fastest-growing neurological disorder in the world [1], and it affects approximately 145,519 people in the UK. PD is a complex, progressive condition with a range of motor and non-motor symptoms [2]. Speech impairments are common in the PD population with a reported prevalence of 68% for patient-perceived problems and 71% for listener-rated speech impairment [3]. In a study of 125 participants with PD [4], 38% placed speech among their top four concerns and, in another study, 29% of participants [5] reported speech problems to be among their greatest present difficulties. Miller et al. [6] noted how changes in communication led to increased physical and mental demands during conversation, an increased reliance on family members and/or carers, and an increased likelihood of social withdrawal. The speech of people with PD is often perceived as sounding quiet and imprecise, creating a potential social barrier to communication [7]. A qualitative study involving 24 people living with PD identified problems with speaking as an activity. The interviewees reported having to think more about speaking; weighing up the value versus the effort of speaking; having negative feelings about speaking; finding that speaking is influenced by different people and places; and having to adjust to the effect of speaking of the disease progression and their medication [8]. Overall, impairments of speech have been recognised to reduce the quality of life of people with PD [7, 9, 10].

Speech and Language Therapy (SLT) for speech difficulties in people with PD in the UK aims to improve communication. Some therapy approaches engage the person with PD in exercises to improve motor skills, others support the communication partnership between the person with PD and their communication partner, while others consider augmentation, or alternative means of communication. Following assessment and discussion with the person with PD, an individually tailored therapy plan is developed to address their needs and those of their family. For the purposes of the PD COMM trial, any of the above will be included in the intervention arm called ‘standard National Health Service (NHS) SLT’. This ‘standard NHS SLT’ is distinct from the other trial intervention arm which comprises Lee Silverman Voice Treatment (LSVT LOUD®) [11]. Within the PD COMM trial two types of SLT will be assessed: standard NHS SLT and LSVT LOUD® [11] against a no-SLT control.

Standard NHS SLT can include any of the above with the therapist selecting from multifaceted therapy components and tailoring these to the needs of the individual, their impairment and participation targets and within the constraints for that particular clinical service [6]. Typically, weekly sessions over 6–8 weeks are prescribed, either individually or in groups [12, 13]. LSVT LOUD® differs from standard NHS SLT in that it is a more prescriptive therapy. The focus of LSVT® is to ‘think loud’; improving phonation and vocal loudness through better vocal fold adduction [14] over an intervention lasting for 16 sessions. The single focus and intensive delivery is used to ‘recalibrate’ the patient, so that they recognise that a voice which sounds too loud to them is necessary for them to be understood by other people. LSVT LOUD® is increasingly being used in the NHS, but in the context of PD COMM, standard NHS SLT excludes the delivery of LSVT®.

A Cochrane review of SLT versus no intervention (last search date 11 April 2011) identified three randomised controlled trials (RCTs) of differing SLT interventions versus no intervention (*n* = 63) [15]. The SLT evaluated varied from: 10 h over 4 weeks of individual therapy focussing on prosodic features of pitch and volume reinforced by visual feedback [16]; 16 h over 4 weeks of LSVT [11]; and 35–40 h over 2 weeks improving loudness and pitch variation, respiration, voice production and intelligibility reinforced by visual feedback primarily in a group setting [17]. The review authors concluded that while outcome measures improved following SLT, the small participant numbers, low RCT quality and the possibility of publication bias, meant that the efficacy of SLT for progressive dysarthria in PD against a placebo or no intervention could not be confirmed or refuted. In another Cochrane review of six trials comparing different theoretical approaches to SLT provision for people with dysarthria (*n* = 159) [18]. All six trials assessed intelligibility and almost all of the results were not statistically significant. The exception to this was for one of the three types of perceptual ratings of speech recordings made in the study by Halpern et al. [19] for which LSVT gave the greater improvement (*n* = 14). Herd et al. [18] concluded that the small number of participants examined, the low methodological quality of the trials evaluated, and the possibility of publication bias resulted in an inability to determine the superiority of any one type of SLT over another. Since these reviews were published, two further RCTs have been reported: the PD COMM Pilot trial [13] (described below) and a trial comparing LSVT LOUD® with LSVT ARTIC® (a second type of LSVT focussing on increased movement amplitude directed predominately to the orofacial-articulatory system, but with the same dosing schedule and intensity) with a no SLT intervention control in people with PD and healthy controls [20]. The latter trial included 64 people with PD and measured sound pressure level (SPL) differences and a modified Communications Effectiveness Index (CETI-M) at 1 and 7 months. LSVT LOUD® significantly increased SPL at 1 and 7 months compared to LSVT ARTIC® and control. Both LSVT groups also showed a greater improvement than control in CETI-M at 1 month, but this difference was not maintained at 7 months. A pilot trial (PD COMM Pilot) randomised 89 people with speech problems into a three-arm, assessor-blinded RCT to assess the feasibility and to inform the trial design of a full-scale RCT [15]. Participants were randomised to either LSVT LOUD®, standard NHS SLT or no intervention control in a 1:1:1 ratio. The pilot trial showed a trend towards improvement in the LSVT LOUD® and SLT groups over the control group at 3 months, but the findings were not powered to give a definitive answer.

## Methods/design

The PD COMM trial protocol can be found on: https://www.birmingham.ac.uk/research/activity/mds/trials/bctu/trials/pd/PD-COMM/investigators/documentation.aspx (last accessed 10 September 2019). The trial received ethical approval on 7 December 2015 by the West Midlands NHS Research Ethics Committee (REC) (15/WM/0443), with protocol version 4.0 (14 November 2018) currently in effect (see the ‘Protocol amendments’ section below for details). The project is sponsored by the University of Birmingham (Research Governance Team, University of Birmingham, [name]).

PD COMM is a multicentre, phase III, three-arm, unblinded RCT where participants are randomised in a 1:1:1 ratio to a no-intervention control group, NHS SLT or LSVT LOUD®.

The primary objective of the trial is to evaluate the clinical and cost-effectiveness of the two types of SLT versus no SLT treatment (no SLT control) for people with PD, but the trial will also compare the two types of SLT (LSVT LOUD® versus standard NHS SLT). Therefore, there will be three comparisons within the trial:
LSVT LOUD® versus no SLT controlStandard NHS SLT versus no SLT controlLSVT LOUD® versus standard NHS SLT

Patient-reported measures are being used to assess the participant’s perception of how their voice impacts on daily activities and their quality of life to assess clinical effectiveness. The quality of life of carers will also be assessed, and a cost-effectiveness analysis will be performed.

### Participant characteristics

People will be eligible for recruitment into the trial if they have idiopathic PD as defined by the 1988 UK PDS Brain Bank Criteria [23]; they, or their carer, report problems with speech or voice when asked and they have no signs of dementia – typically this is determined by the person with a PD clinician as per local practice. Furthermore, they must not have evidence of laryngeal pathology including: vocal nodules, a history of vocal strain or previous laryngeal surgery as such patients may not be suitable for LSVT LOUD®; and have not received SLT for speech- or voice-related problems in the past 2 years, as there is some evidence that benefits of LSVT may persist for 24 months [14].

### Identification, recruitment and randomisation

The trial is designed to align with routine care, thus minimising the burden for people with movement difficulties. Participants will usually be identified during routine clinic appointments with their clinician or Parkinson’s specialist nurse who will inform potentially eligible patients of the trial and provide a copy of the participant information sheet (PIS). The patient will be given time to review the PIS and/or go through it with a member of the team, typically the research nurse, and will be given the opportunity to ask questions. Given the low-risk nature of the trial, and the mobility limitations of the population, participants may join the trial on the same day that they discuss the trial and receive the PIS or may come back at a later date if they prefer.

Following informed consent and completion of the baseline assessment and questionnaires, the participant can be randomised into the trial. Prior to randomisation, the team will check the availability of speech and language therapists at that site. Randomisation may be deferred if the SLT intervention cannot be initiated within the set time frames – however, the participant’s baseline questionnaire needs to be completed within 2 weeks prior to randomisation, so this should be factored in to any planned delay of a patient’s randomisation. Typically the research nurse, will obtain informed consent and randomise the patient into the trial and liaise with the speech and language therapist to ensure that SLT (should they be randomised to therapy) starts within the required time frame.

Following informed consent and completion of all baseline data collection, participants will be randomised at the level of the individual via a central secure web-based randomisation system at the Birmingham Clinical Trials Unit (BCTU) to ensure concealment of the next treatment allocation. Typically, randomisation will be performed by the research nurse. The randomisation process will use a minimisation procedure with a random element. The following minimisation variables will be used:
Age (≤ 59, 60–70, > 70 years)Disease severity measured using the Hoehn and Yahr [24] staging (1.0–2.5, 3.0–5.0) andSeverity of speech measured using the Voice Handicap Index (VHI) [25] total score (≤ 33, mild 34–44, moderate 45–61, severe > 61)

Once randomised into the trial, NHS SLT should start within 4 weeks and LSVT LOUD® should start within 7 weeks to enable the intervention to be completed prior to the primary end point (at 3 months post randomisation). The trial will last for 77 months. Recruitment will take place in approximately 42 sites around the UK (see Table 1).

**Table 1 Tab1:** Participating sites and principal investigators (PIs)

Trust	PI
Aneurin Bevan University Health Board	[name]
Basildon and Thurrock University Hospitals NHS Foundation Trust	[name]
Betsi Cadwaladr University Health Board	[name]
Blackpool Teaching Hospitals NHS Foundation Trust	[name]
Brighton and Sussex University Hospitals NHS Trust	[name]
Cardiff and Vale University Health Board	[name]
Central London Community Healthcare NHS Trust	[name]
East Cheshire NHS Trust	[name]
Gloucestershire Hospitals NHS Foundation Trust	[name]
Great Western Hospitals NHS Foundation Trust	[name]
Guy’s and St Thomas’ NHS Foundation Trust	[name]
Harrogate and District NHS Foundation Trust	[name]
Heart of England NHS Foundation Trust (now University Hospitals Birmingham NHS Foundation Trust)	[name]
Homerton University Hospital NHS Foundation Trust	[name]
Hywel Dda University Health Board	[name]
Lancashire Teaching Hospitals NHS Trust	[name]
Leeds Teaching Hospitals NHS Trust	[name]
London North West Healthcare NHS Trust	[name]
NHS Ayrshire and Arran	[name]
NHS Dumfries and Galloway	[name]
NHS Forth Valley	[name]
NHS Greater Glasgow and Clyde	[name]
NHS Highland/Argyll and Bute	[name]
NHS Lanarkshire	[name]
NHS Lothian	[name]
NHS Tayside	[name]
Norfolk and Norwich University Hospitals NHS Trust	[name]
Norfolk Community Health and Care NHS Trust	[name]
North Bristol NHS Trust	[name]
Northern Lincolnshire and Goole NHS Foundation Trust	[name]
Pennine Acute Hospitals NHS Trust	[name]
Powys Teaching UHB	[name]
Royal Devon and Exeter NHS Foundation Trust	[name]
Sandwell and West Birmingham Hospitals NHS Trust	[name]
St Helens and Knowsley Hospitals NHS Trust	[name]
Taunton and Somerset NHS Foundation Trust	[name]
The Walton Centre NHS Foundation Trust	[name]
Torbay and South Devon NHS Foundation Trust	[name]

#### Interventions

##### Standard NHS SLT

Standard NHS SLT is not prescriptive and does not have standard content or dosage. It is, therefore, not possible to predict the number of sessions that will be provided. A survey of current UK SLT practice for PD [12] reported a median dose of six sessions delivered over 42 days. The PD COMM Pilot trial found the median dose to be six sessions (range 1–14) over an average of 9.6 weeks (standard deviation 6.1 weeks) [13].

Treatment is typically tailored to the individual’s level of difficulty or dysarthria severity and their interests as individual need and clinical constraints. Treatment will be individualised to suit each participant’s needs as per local practice. It may include impairment-based interventions, compensatory interventions and augmentative and alternative communication (ACC) strategies aimed at improving communication and participation. The participant’s family/carer(s) may be involved. Therefore, the NHS SLT arm will encompass any SLT interventions that are not LSVT LOUD® as per the LSVT LOUD® protocol.

Treatments targeted at impairment level may include exercises focussed on improving capacity, control and co-ordination of respiration, techniques for improving phonation intensity and co-ordination with respiration (but not LSVT LOUD®), and exercises to improve the range, strength and speed of the articulatory muscles [16, 17]. Behavioural therapy may include interventions aimed at reducing prosodic abnormality [26, 27] such as exercises targeting pitch, intonation, stress patterns and volume variation [16, 17, 26–28], and techniques to address the overall rate of speech [16, 17] including the use of therapeutic devices such as pacing boards [29, 30]. AAC strategies such as topic and alphabet supplementation through communication books and boards may be employed [31] along with AAC devices such as voice amplifiers, delayed auditory feedback systems and masking devices [32–34]. The practice of pitch-limiting voice treatment [35] may also be utilised within the standard SLT intervention.

The above methods may include techniques used in LSVT LOUD®, e.g. vocal intensity exercises, but will be distinct by the individualised treatment, other SLT strategies, lower intensity of delivery and (potentially) the use of group intervention.

Dose will be determined by the therapist reflecting participants’ individual needs, but the duration is unlikely to exceed 12 weeks of treatment. Sessions will be conducted by a suitably trained speech and language therapist or therapy assistant on a one-to-one or group basis per participant need and local practice. Sessions may take place in out-patient clinics, the participant’s home or in the community.

##### LSVT LOUD®

The LSVT LOUD® intervention is prescriptive and consists of four 50-min sessions per week delivered over 4 weeks [36]. Each session follows a similar structure: 25 min of repeated and intensive maximum-effort drills, and 25 min of high-effort speech production tasks [36]. Participants will also be set 5 to 10 min of home-based practice tasks on treatment days, and up to 30 min of home-based practice tasks on non-treatment days [37].

Content will consist of repeated repetitions of sustained ‘ah’ phonation, maximum fundamental frequency-range high- and low-pitch glides, and functional sentence repetition for the first half of each session, and exercises using speech production hierarchy that progresses throughout duration of the treatment programme (single word, phrases, sentences, paragraph reading, conversation) during the second half of the sessions [37]. Throughout all of the sessions, the focus of the intervention will be to ‘think loud’, maintaining the vocal loudness produced during vowel phonation throughout all other tasks during the treatment [36].

Sessions will be conducted by a suitably trained speech and language therapist or therapy assistant on a one-to-one basis. Sessions may take place in out-patient clinics, the participant’s home or remotely using tele-LSVT software. Once the exercises have been established, LSVT LOUD® may be delivered using the LSVT companion software for a proportion of the time, in line with local practice.

##### Control

The control group will not receive any SLT for their speech for 12 months, unless it becomes clinically necessary. At the end of 12 months, participants will be treated per local practice. If the participant needs SLT prior to 12 months, with their continued consent, they will remain in the trial and be followed up as usual and included in the trial analyses.

Participants are free to withdraw from the trial at any time or they may agree to continue in the trial but not comply with treatment. In the latter case they will continue to be followed up as per the protocol and the data will be analysed according to the group that they were randomised to (intention to treat).

#### Outcomes

Following the analysis of PD COMM Pilot, the design of the trial was refined to reduce the burden on participants and speech and language therapists by excluding the battery of vocal assessments and the Voice-related Quality of Life [38] questionnaire.

### Primary outcome

The primary outcome measure for the trial is patient reported Voice Handicap Index (VHI) [25] total score at 3 months.

There was some discussion about the choice of primary outcome, as most previous trials had used vocal loudness. The VHI was chosen given that it is patient-reported, brief, (and from the pilot trial) well-completed and, in our view, better reflects the focus of the trial. Alongside the VHI, a battery of patient-reported outcomes (PROs; see the ‘Secondary outcomes’ section) are being collected, which cover a range of other important areas. In the pilot trial, extensive vocal assessments were carried out alongside the PROs. We decided not to undertake vocal assessments within the PD COMM trial as (1). the additional time involved was prohibitive; (2). there was concern that since one of the trial interventions (LSVT LOUD®) specifically focussed on vocal loudness that the results might be skewed in favour of this intervention and (3). the focus of the trial was on the participants self-perception of functional communication rather than vocal loudness.

### Secondary outcomes

Patient reported: Subscales of the VHI [25]; Parkinson’s Disease Questionnaire-39 (PDQ-39) [39]; Questionnaire on Acquired Speech Disorders (QASD) [40]; EuroQol-5D (5-level version) [41]; ICEpop Capabilities Measure for Older Adults (ICECAP-O) [42]; resource utilisation; and adverse events (AEs).

Carer reported: Carer quality of life (Parkinson’s Disease Questionnaire–Carers) [43].

### Other data collected includes

Demographics including height (baseline only), weight and Hoehn and Yahr stage (at baseline and 12 months) [24]; PD medication; Abbreviated Mental Test [44] (intervention arms only), therapy logs including home-based therapy diaries, NHS therapy notes and a global rating scale (Transition item).

#### Adverse events

A risk assessment of the PD COMM trial has been performed with the SLT interventions considered to be of low risk. From the literature, the only reported AE associated with the interventions was a small increased risk of vocal strain or abuse; however, none were reported in the PD COMM Pilot trial. This risk will be minimised: speech and language therapists are trained to identify and rehabilitate vocal strain so, if present, the therapist will be able to identify and address it. No other risks are expected to arise from taking part in the trial. It is, therefore, reasonable to collect only targeted AEs.

For participants in either therapy arm, any vocal strain or abuse believed to be associated with treatment will be identified by the therapists at the participants’ therapy session and will be reported in the AE log.

In all trial arms, BCTU will also check the participant-reported resource usage form to ensure that no vocal strain or abuse has occurred following participants reporting out-patients appointments with ear, nose and throat (ENT) specialists. At the 12-month clinical visit, the medical professional will also check whether any AEs have occurred since entering the trial.

Serious adverse events (SAEs) are events that cause death, are life-threatening, require or extend an existing hospitalisation, result in persistent or significant disability or incapacity; or, are otherwise considered medically significant by the investigator. SAEs that are not related to vocal strain or abuse are excluded from expedited notification during the course of the trial and will be collected in the resource usage and 12-month clinical case report form (CRF).

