**Assessments**					
Baseline case report form		✓			
VHI; PDQ-39; QASD; EQ-5D-5 L; ICECAP-O		✓	✓	✓	✓
Resource Usage Questionnaire			✓	✓	✓
Global rating score (Transition item)			✓		
PDQ-Carer		✓	✓	✓	✓
Adverse event log			✓^c^		
12-month case report form					✓

^a^Following each therapy session for participants in the two SLT treatment arms only

^b^Completed at home by the participant as recommended in their SLT therapy session

^c^Only required for participants randomised to a treatment arm

Key: *EQ-5D* EuroQol 5-dimension, 5-level questionnaire, *ICECAP-O* ICEpop Capabilities Measure for Older Adults, *QASD* Questionnaire on Acquired Speech Disorders, *PDQ-39* Parkinson’s Disease Questionnaire-39, *SLT* Speech and Language Therapy, *VHI* Voice Handicap Index

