### Secondary outcome analyses

The majority of the secondary outcome measures (e.g. PDQ-39) are continuous measurements and will be analysed in a similar way to that described for the primary analysis: a linear regression analysis adjusting for relevant baseline score and all of the minimisation variables (baseline VHI, age and severity of PD). As per the primary outcome, the primary analysis for the secondary outcomes will be based on the 3-month data.

To assess whether any treatment effect is maintained, participant- and carer-completed questionnaires are also being collected at 6 and 12 months post randomisation. Data collected at 6 and 12 months will be analysed using the same methods as described above. Further analysis using a repeated measures model will also be performed using all data over the 3-, 6- and 12-month assessment points.

A global rating scale (Transition item) will be completed by the participant and carer separately at the 3-month time point. This data will be used to calculate an MCID for the VHI in this population.

Adverse events and safety data will be summarised descriptively by treatment arm, and the number of events and percentage of participants experiencing any AE reported. It is not expected that there will be many AEs as a result of the intervention, but the number of participants reporting an AE will be compared using a chi-squared test, with relative risks and 95% confidence intervals reported (if appropriate).

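### Vocal strain, the one targeted adverse event, has an attribution condition in the therapists' log but none in the ENT and 12-month checks, and one undivided AE comparison is planned

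*Protocol article*

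**What the plan says.** The Adverse events section names vocal strain or abuse as the only adverse event linked to the interventions in the literature, notes that the pilot had none, and limits collection accordingly: "It is, therefore, reasonable to collect only targeted AEs". It describes three routes of capture.

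- **Therapist's AE log, therapy arms only:** "any vocal strain or abuse believed to be associated with treatment will be identified by the therapists" at the therapy session and reported in the log. A footnote to the AE log row of Table 2 confirms the restriction: "Only required for participants randomised to a treatment arm".
- **ENT check, all arms:** the trials unit reviews the resource usage form "to ensure that no vocal strain or abuse has occurred following participants reporting out-patients appointments with ear, nose and throat (ENT) specialists".
- **12-month clinic visit:** "the medical professional will also check whether any AEs have occurred since entering the trial".

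For the analysis, Secondary outcome analyses plans a descriptive summary by arm with "the number of events and percentage of participants experiencing any AE reported". It adds that "the number of participants reporting an AE will be compared using a chi-squared test", with relative risks and 95% confidence intervals if appropriate. It mentions no division by route of capture or by relation to treatment.

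**The concern.** The first route has a filter that the other two lack. The wording implies, without saying so, that the belief in question is that of the treating therapist, who is unblinded. Hoarseness that the therapist ascribes to a cold or to the disease itself would not qualify for the log. The same episode would qualify if it surfaced through an ENT appointment or at 12 months.

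Two things are at stake. The absolute rate of the only named risk in the therapy arms may be too low. The LSVT LOUD versus NHS SLT relative risk, one of the trial's three comparisons, may also partly reflect differences in attribution. The two settings differ enough to make this plausible: the LSVT LOUD section describes 16 sessions of maximum-effort voice drills, while the Standard NHS SLT section describes tailored therapy with a pilot median of six sessions, which may include communication aids.

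This is separate from the control arm having no AE log. Extending the log to controls would leave the filter in place.

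**Working it through.** **Case definitions side by side**

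| Route | Arms | Attribution condition |
|---|---|---|
| Therapist's AE log | Two therapy arms | Yes: believed to be associated with treatment |
| ENT check from resource usage form | All | None |
| 12-month clinic check | All | None |
| Planned summary and comparison | By arm | No split by route or relatedness |

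**The plan's own figures.** The article gives no AE rate and no power for AEs. The only figure to reproduce is the sample size, which supplies the denominator. A 10-point difference, SD 26.27, two-sided alpha 0.01 and 80% power give 162.9, so 163 per arm, by the two-sample t test. Then 163 / 0.9 = 181.1, so 182 per arm, and 3 × 182 = 546. All three stated figures reproduce.

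**Model.** Let p be the true strain rate, a the probability that an episode is attributed to treatment and logged, and r the probability that an unattributed episode is recovered by the ENT or 12-month check. Then

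observed rate = p × [a + (1 − a) × r].

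The article gives none of p, a or r, so all values below are assumptions.

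**Relative risk with equal true rates.** p cancels, leaving [a + (1 − a)r] for LSVT LOUD over the same expression for NHS SLT.

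| Attribution, LSVT LOUD v NHS SLT | r = 0 | r = 0.3 | r = 0.6 |
|---|---|---|---|
| 0.9 v 0.9 | 1.00 | 1.00 | 1.00 |
| 0.9 v 0.6 | 1.50 | 1.29 | 1.14 |
| 0.9 v 0.5 | 0.90/0.50 = 1.80 | 0.93/0.65 = 1.43 | 0.96/0.80 = 1.20 |
| 0.9 v 0.3 | 3.00 | 1.82 | 1.33 |
| 0.6 v 0.9 | 0.67 | 0.77 | 0.88 |

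The last row shows that the direction is not fixed either.

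**Counts.** At p = 3% and r = 0, attribution of 0.9 v 0.5 gives 0.03 × 0.9 × 182 = 4.9 against 0.03 × 0.5 × 182 = 2.7, a gap of about 2 participants.

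**Absolute rate.** If attribution is 0.5 in both arms the relative risk stays at 1.00, but the share of true episodes captured is 50% at r = 0, 0.5 + 0.5 × 0.3 = 65% at r = 0.3, and 0.5 + 0.5 × 0.6 = 80% at r = 0.6.

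**Chance of a false p < 0.01.** By the normal approximation this is Φ(difference / SE − 2.576). For p = 3%, 0.9 v 0.5 and r = 0, the rates are 0.027 and 0.015. SE = √[(0.027 × 0.973 + 0.015 × 0.985) / 182] = 0.0150, so Φ(0.80 − 2.58) is about 4%. At p = 2% and 5% the same formula gives about 3% and 6%. For 0.9 v 0.6 and r = 0 it gives about 2% at p = 2% and 3% at p = 5%. The extreme case of 0.9 v 0.3 with r = 0 gives about 6% and 18%. The approximation is rough at such small counts.

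**The case against.** The strongest reply is that the trial has other records. Treatment dose and fidelity has therapists complete a record form at each session as well as their usual NHS notes, and a pseudo-anonymised version of the notes goes to the research team. Data collection confirms that logs and notes reach the trials unit. The 12-month check is unfiltered. A reader might infer that unattributed strain is lost beyond recovery. The documents do not support that: there is no structured AE entry, but a source record may exist. Even so, recovery is not assured. The stated use of the redacted notes is the intervention description, and no AE review of them is described. The ENT route needs a reported ENT appointment, although therapists are expected to deal with strain themselves. The 12-month check is a single look back over the year.

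A second reply is that the log rule is identical in both therapy arms. A reader might infer that the LSVT LOUD versus NHS SLT comparison is biased. That follows only if attribution or recovery differs, which nothing in the article establishes. NHS SLT may itself include vocal intensity exercises, and therapists are described as trained to recognise strain. This reply stands: the distortion is possible, not demonstrated.

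Third, the ENT sentence describes a check rather than a counting rule, and pooling of the routes is inferred from the analysis text. Also, belief in an association is weaker than belief that treatment was the cause. Both cautions are accepted. The full protocol, the case report form and the analysis plan are not shown and may classify events further. They could separate recorded events, but an analysis plan cannot restore an episode that was recorded nowhere.

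Finally, few events are expected, and targeted collection is a reasoned choice based on a risk assessment. That limits the importance of the point; it does not reconcile the definitions.

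**Conclusion.** The point holds in a limited form and is minor. The article states a capture rule that puts an attribution condition on one route and none on the other two, and plans a single AE comparison without a split. The therapy-arm rate of the only named risk can be understated even when both arms behave alike. The LSVT LOUD versus NHS SLT relative risk can be distorted if attribution differs: 1.80, 1.43 or 1.20 under an assumed 90% against 50% with recovery of 0%, 30% or 60%, and 1.00 under equal attribution and recovery. Neither the size nor the direction of any real distortion is known.

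A reader might go further and expect a spurious significant safety finding or damage to the main result. Neither is supported. At assumed true rates of 2% to 5% with attribution of 90% against 50%, the chance of a false p < 0.01 is about 3% to 6% without recovery; only a far wider gap in attribution raises it materially. The primary outcome is the VHI total score at 3 months, which this does not touch.

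**What to change.** In the Adverse events section, remove the attribution condition from the therapist's log. Have therapists log every episode of vocal strain or abuse seen or reported at a session, with the believed relation to treatment as a separate field. State the same definition for the ENT and 12-month checks. In Secondary outcome analyses, report all events and treatment-related events separately, and show counts by source.

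The cost is one deleted qualifier, one added field and a few more entries, some of them unrelated. The sample size stays at 546. The real drawback is timing: the Discussion reports 329 participants recruited by 10 September 2019 (329/546 = 60%), so the definition would change part-way through recruitment. The change should be dated and reported. The therapy notes already held could be checked for vocal strain among earlier participants, within the limits of what therapists wrote down.
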